#### Secondary Objectives:

- Quantitative: Assess structural and functional changes in the brain (e.g., global and local brain volume, white matter changes), quality of life, mobility, motivation, lifestyle factors, stress, care dependence, (instrumental) activities of daily living, changes in medication, endogenous/biological factors (i.e., the significance of DNA variants, DNA methylation processes, or changes in gene expression related to dementia), behavioral problems, caregiver burden, activity level, and arm strength, as well as evaluate potential depressive symptoms and utilize the collected data for the development of a decision support system.
- Quantitative: Investigate the usability and acceptance regarding the use of the training program.
- Qualitative: Conduct supplementary interviews (focus groups and individual interviews) on usability.

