###### Exclusion Criteria

- The PwD has participated in a clinical study in the 3 months before the baseline visit.
- The PwD is expected to be unable to complete the study.
- Any of the following signs on the brain MRI:

- ✓ Infarct near major vessels
  - ✓ More than one lacunar infarct, defined as a focal lesion in the CSF signal intensity with a diameter of less than 1.5 cm in all spatial directions.
  - ✓ A lacunar infarct in a strategically important region such as the thalamus, hippocampus in both hemispheres, or the caudate nucleus.
  - ✓ Confluent lesions of the deep white matter (Fazekas Score 3).
  - ✓ Other focal lesions that could be responsible for the patient's cognitive status (e.g., infections, space-occupying lesions, normal pressure hydrocephalus).
  - ✓ The PwD has undergone or has a planned operation with general anesthesia within the last 3 months before the baseline visit or during the study period.
- The PwD has had or is currently undergoing clinically significant immunomodulatory treatment or will receive such treatment in the future.
  - The PwD has a cancer diagnosis (last treatment  $\leq 5$  years before the baseline visit).
  - The PwD has had a myocardial infarction within the last 2 years before the baseline visit.
  - The PwD has hepatitis B, C, HIV, or syphilis.
  - The PwD has an active infectious disease.
  - The PwD suffers from a systemic disease that is likely to cause rapid deterioration or compromise safety:
    - ✓ Uncontrolled heart failure (NYHA>3)
    - ✓ BMI>40
    - ✓ Poorly controlled diabetes
    - ✓ Severe renal insufficiency
    - ✓ Chronic liver disease
    - ✓ Other clinically relevant systemic diseases.
  - The PwD suffers from hypothyroidism. Persons with treated hypothyroidism may participate if they have had stable therapy for more than 3 months before the baseline visit.

- The PwD suffers from a psychiatric illness, such as schizophrenia, psychotic disorders, or bipolar disorder.
  - ✓ The PwD currently has a depressive episode (Geriatric Depression Scale GDS  $\geq 6$  at baseline visit) or major depression within the last 2 years.
- The PwD has a metabolic or toxic encephalopathy or dementia due to general medical conditions.

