#### 4.3.1. Study Procedure

In the first step, a prescreening of potential participants is conducted using a shortened list of inclusion and exclusion criteria through the SVDL and the Austrian Red Cross. Potential patients are then subjected to a clinical-neurological examination (including vital signs), a blood draw, and a cognitive assessment (performance tests and questionnaires) at the Medical University of Graz, Department of Neurology, at Time Point T0-a (see **Table 1**). Based on the clinical-neurological examination and cognitive assessment, it will be determined whether the participant needs a structural and functional magnetic resonance imaging (MRI) (T0-b) to medically confirm an early-stage Alzheimer's diagnosis. Simultaneously, the relatives/informal caregivers will be interviewed regarding caregiving and personal data. For participants with Alzheimer's dementia who are included in the study, additional data (see **Table 1**) will be collected at 6 months (T1) and 12 months (T2). After the 1.5-year tablet training, a clinical-

neurological examination, including blood draw, a cognitive assessment, including questionnaires, and a structural and functional MRI (T3) will be performed again.

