| Measurement of arm strength               | Arm strength                                                                                                                                                                                                                                                                                                                                                                                                                    | PwD:
Self                           | 2 min.                                        | T0-a, T3                                                                |
| Psychiatric factors                       | Neuropsychiatric Inventory (NPI)                                                                                                                                                                                                                                                                                                                                                                                                | Proxy by an informal caregiver         | 10                                            | T0-a, T3                                                                |
| Depression or depressive symptoms         | GDS (The Geriatric Depression Scale)                                                                                                                                                                                                                                                                                                                                                                                            | PwD:
Self                           | 5 min                                         | T0-a, T3                                                                |

|                                               |                                     |                                                                                 |                                                                      |                                            |
|-----------------------------------------------|-------------------------------------|---------------------------------------------------------------------------------|----------------------------------------------------------------------|--------------------------------------------|

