According to the table, there are three measurement time points at the University Clinic for Neurology/Neuroradiology. At the first time point, the person with dementia undergoes a clinical neurological examination, a neuropsychological examination, and a blood draw. The total examination duration will be about two and a half hours. If the person with dementia still meets the strict inclusion and exclusion criteria after this examination day, they will be invited to a further appointment. At the second examination appointment, an MRI will be performed. The MRI takes approximately 45 minutes. At the end of the tablet-based training, after 1.5 years, all examinations will be repeated (duration: about three hours).

Between the different medical and psychological examinations, breaks will be provided, and a break will be given upon the patient's request. Additionally, time will be allocated for a meal. To relieve the patient and their informal caregivers on the day of the examinations at the University Clinic for Neurology, questionnaires that do not require neuropsychological training from the examiner will be filled out by the patients together with their informal caregivers or a staff member from the SVDL or ÖRK at home without time pressure. Clinical tests will be conducted by psychologists. The questionnaires will be provided at the beginning, after 6, 12, and 18 months, with each filling time taking less than half an hour for both the patient and the informal caregiver.

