## **4.5. Statistics**

### Quantitative Part

The data will be analyzed using IBM SPSS version 24. The significance level is set at  $\alpha = 0.05$ . Descriptive statistics will be presented as mean and standard deviation or as median and quartiles, depending on the type of distribution. Absolute and relative frequencies will be used to describe categorical data. To address the primary research question—whether tablet-based training has a positive effect on cognition—both the primary outcome (performance in the neuropsychological test battery, NTB, global score) and secondary outcome parameters (sub-tests of the NTB and other neuropsychological assessments) will be compared between the intervention group (IG) and control group (CG) using ANCOVA (adjusted for multiple comparisons). Additionally, total brain volume, the volume of brain lobes, hippocampal volume, cerebral microstructure, and functional connectivity will be measured and compared between groups. Other secondary outcome parameters will also be compared between groups using ANCOVA. Pre-post comparisons (ANOVA repeated measures) will provide insights into changes over time. Analyses will be adjusted for age, gender, comorbidities, and education level.

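### The GDS reading that excludes patients scoring 6 or more is also the only pre-training GDS, so the planned pre-post GDS change is biased upward in expectation, by an amount the protocol does not let one fix

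*Protocol*

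**What the plan says.** **Selection.** The exclusion criteria in Protocol section 4.2.2.1 rule out a patient on the GDS score itself: "The PwD currently has a depressive episode (Geriatric Depression Scale GDS", with a threshold of 6 or more, "at baseline visit) or major depression within the last 2 years".

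**Measurement.** Table 1 in section 4.4.1 lists "GDS (The Geriatric Depression Scale" as self-report by the person with dementia, at T0-a and T3 only.

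**Timing of the eligibility decision.** Section 4.3.1 describes "a cognitive assessment (performance tests and questionnaires) at the Medical University of Graz, Department of Neurology, at Time Point T0-a". The text after Table 1 invites a patient to the MRI appointment only if he or she "still meets the strict inclusion and exclusion criteria after this examination day". T0-a is thus the visit on which selection is made.

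**Outcome and analysis.** Section 3 includes among the secondary quantitative objectives "as well as evaluate potential depressive symptoms". Section 4.5 plans two analyses that cover it: "Other secondary outcome parameters will also be compared between groups using ANCOVA", and "Pre-post comparisons (ANOVA repeated measures) will provide insights into changes over time". Neither sentence makes an exception for an outcome that was also used to select patients.

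**The concern.** A pre-post comparison measures change fairly only if the first reading was not itself the filter for entry. Here it was. A patient whose T0-a score happened to fall below his or her usual level stays in; one whose score happened to fall above it, to 6 or more, is removed. Among those who stay, chance errors at T0-a are on average negative. They do not persist to T3, so the mean drifts back up.

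Two results would be open to misreading: a rise in mean GDS over 18 months within an arm or over both arms, and a share of patients at 6 or more that starts at 0% by design and can only go up. Either could be reported as emerging depressive symptoms when part or all of it comes from the entry rule.

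**Working it through.** The protocol states no figure for GDS change, so there is none to reproduce.

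**From the protocol:** entry requires T0-a GDS of 5 or less; readings at T0-a and T3 only; 110 patients planned per arm, 220 in all; alpha 0.05.

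**Assumed, because the protocol is silent:** a 0-15 version of the scale; screened population with mean 2, 3 or 4 and SD 2, 2.5 or 3 respectively; reliability r of 0.70-0.85; no dropout; no true change.

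**Step 1, closed form.** For a bivariate normal score with no true change, kept if below the rounding boundary 5.5:

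expected rise = (1 - r) x SD x phi(a) / Phi(a), where a = (5.5 - mean) / SD.

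- Mean 2, SD 2: a = 1.75; phi/Phi = 0.0863/0.9599 = 0.090; 4% excluded. With r = 0.85: 0.15 x 2 x 0.090 = 0.03.
- Mean 3, SD 2.5: a = 1.00; phi/Phi = 0.2420/0.8413 = 0.288; 16% excluded. With r = 0.70: 0.30 x 2.5 x 0.288 = 0.22.
- Mean 4, SD 3: a = 0.50; phi/Phi = 0.3521/0.6915 = 0.509; 31% excluded. With r = 0.70: 0.30 x 3 x 0.509 = 0.46.

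The result is positive whenever r is below 1 and some screened patients score 6 or more.

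**Step 2, simulation on the score scale.** Stable true score plus independent error at T0-a and T3, rounded, clipped to 0-15, kept if T0-a is 5 or less. Expected t = rise / SD of change x sqrt(n).

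| Screened mean, SD | r | Excluded | Rise | SD of change | t, n=110 | t, n=220 | 6 or more at T3 |
|---|---|---|---|---|---|---|---|
| 2, 2 | 0.85 | 4% | 0.03 | 1.04 | 0.3 | 0.4 | 2% |
| 2, 2 | 0.70 | 4% | 0.06 | 1.40 | 0.4 | 0.6 | 3% |
| 3, 2.5 | 0.85 | 16% | 0.12 | 1.28 | 1.0 | 1.4 | 6% |
| 3, 2.5 | 0.70 | 16% | 0.23 | 1.73 | 1.4 | 1.9 | 9% |
| 4, 3 | 0.85 | 31% | 0.24 | 1.52 | 1.7 | 2.4 | 11% |
| 4, 3 | 0.70 | 31% | 0.47 | 2.04 | 2.4 | 3.4 | 16% |

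Last row: 0.472 / 2.041 x sqrt(110) = 2.43, and x sqrt(220) = 3.43.

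**Step 3, sensitivity to shape.** With a skewed 0-15 score (beta-binomial margins, screened means 2-5, 12-40% excluded), the rise is 0.34-0.92 points at a latent correlation of 0.7 and 0.07-0.17 at 0.95. The direction was upward in every scenario; the size depends heavily on the inputs.

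**Step 4, the between-arm comparison.** In the skewed model (screened mean 3, latent correlation 0.7, 110 per arm, no effect and no change), ANCOVA on T3 GDS adjusted for T0 GDS rejected in 5.05% of simulated trials, with a mean arm difference of -0.01 points. In the same trials the paired pre-post test on all 220 was falsely significant in about 93%, with a mean rise of 0.51 points. The entry rule treats both arms alike, so the drift cancels between them.

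**The case against.** The structure is not in dispute. The case against rests on weight.

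- **Size.** Every magnitude is assumed. At 110 patients, five of the six scenarios tabulated have an expected t below 1.96, so a single-arm test would more often than not show nothing. A prescreening on a shortened criteria list precedes T0-a, and recent major depression is a separate exclusion; few high scorers may reach T0-a, which is the near-zero case. Dropout lowers it further: with 60-80 completers per arm, the largest t of 2.4 becomes 1.8-2.1. All of this stands, and is why the range starts near zero.
- **The sound analysis is already planned.** Section 4.5 has the between-arm ANCOVA for secondary outcomes. This stands too.
- **A caveat on interpretation belongs in the SAP.** This carries less. The protocol does not merely leave a detail open; it says that pre-post comparison informs on change over time, and for the GDS its own entry rule undermines that.
- **Low consequence.** The study calls itself exploratory, the pre-post sentence does not name the GDS, and depressive symptoms are one item in a long list of secondary objectives. This stands.

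Two stronger readings are tempting. A reader might infer that the trial will show rising depression by construction. The documents support only an upward bias in the expected change; the observed change may be small, or offset by real improvement. A reader might also infer that the trial could wrongly conclude that training fails to protect mood. That is a between-arm question, and neither the ANCOVA nor the group-by-time term is biased by the entry rule.

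**Conclusion.** The point holds for the within-arm and pooled time effect of the GDS, and only there. The expected pre-post change is biased upward, and the share at 6 or more starts at 0% by design.

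Under the step 2 assumptions the spurious rise lies between about 0.03 and 0.47 points. The expected t runs from about 0.3 to 2.4 in one arm of 110, and reaches about 3.4 if both arms are pooled. Other distribution shapes or retest correlations move these limits, and the protocol offers nothing to choose among them. The direction needs only imperfect retest correlation and some screened patients at 6 or more.

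This is a minor point: a planned analysis that would be misread for one secondary outcome, with no bearing on the primary outcome, the treatment comparison or the choice of eligibility threshold.

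**What to change.** Add one sentence to section 4.5. For the GDS, the conclusion rests on the between-arm comparison: the ANCOVA already planned, with T0 GDS named as a covariate (the adjustment list there gives age, gender, comorbidities and education level), or the group-by-time term. The within-arm or pooled time effect and new crossings of 6 are not interpreted as a change in depression.

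This needs no new data and leaves the entry criterion as it is. The cost is that the within-arm GDS trend is given up as evidence about mood over time; it can still be shown descriptively with that caveat.

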| Global Cognition                          | MoCA (Montreal Cognitive Assessment)                                                                                                                                                                                                                                                                                                                                                                                            | PwD:
Proxy by data collector        | 15 Min.                                       | T0, T1, T2, T3                                                          |
| (Instrumental) activities of daily living | Disability Assessment for Dementia Scale (DAD)                                                                                                                                                                                                                                                                                                                                                                                  | PwD:
Proxy by an informal caregiver | 15 min                                        | T0-a, T3                                                                |
| Executive functions/cognitive control     | 
 
MIRA (Mobile Instrumental Review of Attention): Analysis of gaze behavior with an eye tracker on/in the tablet PC using specific interactive ("serious game") exercises:
 
Trail Making Test A, B
 
Anti-Sakkadentest
 
Go/Nogo Test
 
Spot-the-difference
 
 
Test of Attentional Performance (TAP): Sustained attention, executive functions
 | PwD:
Autonomous through Eye-Tracker | Ongoing during tablet-PC training (voluntary) | Every 2 weeks on the tablet with the MAS trainer ("mandatory exercise") |

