## **4.6. Ethical Considerations**

### **4.6.1. Informed Consent**

Only individuals who provide prior written informed consent will be included in the study. For participants with dementia who have a representative or legal guardian, written informed consent will be obtained from these representatives. All participants can withdraw from the study at any time without providing reasons. All examinations, except for blood draws, are non-invasive. Additionally, all procedures, including the 3T MRI, are conducted in clinical routine. Genetic analyses are performed in accordance with legal

requirements. The genetic analyses are conducted solely for scientific purposes and only with the written consent of the donor. All samples are processed anonymously and coded without names. Samples can only be linked to the University Clinic for Neurology with the name of the donor.

If results from genetic analyses are shared, measures will be taken to ensure that the donor cannot be identified by the collaborating centers. Except for blood draws, no harm or burden is anticipated for participants. The benefit-risk ratio is therefore considered to be high.

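### For the MoCA and the AES schedule with interim visits, repeated-measures ANOVA either deletes people with a missed visit or ignores the 6- and 12-month data; a mixed model would use them

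*Protocol*

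**What the plan says.** Section 4.5 (Quantitative Part) fixes the software, "The data will be analyzed using IBM SPSS version 24", and gives change over time one sentence: "Pre-post comparisons (ANOVA repeated measures) will provide insights into changes over time". It does not say which visits enter that analysis or whether group is a factor in it.

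The effectiveness question is handled separately. The "primary outcome (performance in the neuropsychological test battery, NTB, global score") and the secondary outcomes "will be compared between the intervention group (IG) and control group (CG) using ANCOVA (adjusted for multiple comparisons"). The analyses are adjusted for age, gender, comorbidities and education.

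On timing, section 4.3.1 states that additional data "will be collected at 6 months (T1) and 12 months (T2"). Table 1 shows which outcomes this concerns:

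- **T0, T1, T2 and T3:** "MoCA (Montreal Cognitive Assessment") and one of two schedules in the AES row. The order of entries suggests self-rating at T0 and T3, and caregiver rating at all four visits.
- **Baseline and T3 only:** the NTB, MMSE, TAP, DAD, NPI, GDS, TUG, MRI, DEMQOL, care dependency, PAL, ZBI and PSS-10.
- **Every six months, but tied to tablet training:** FAM.

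Follow-up is 1.5 years, and section 4.6.1 allows free withdrawal: "All participants can withdraw from the study at any time without providing reasons". No expected dropout rate is given.

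**The concern.** Classical repeated-measures ANOVA, as run in the SPSS general linear model, works on complete rows. A participant with one missing value among the visits analysed is deleted, together with every value that was collected. Over 18 months in a progressive dementia, missed visits and dropout must be expected, and those who leave may well be those who are declining.

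The sentence leaves two readings for the MoCA and the four-visit AES. If all four visits enter, people are lost even when they attend T3. If pre-post means T0 against T3, nobody is lost for missing T1 or T2, but the 6- and 12-month values contribute nothing. Those values show how a person was doing before leaving. Either way, collected data on global cognition and apathy go unused, and the result describes completers only.

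**Working it through.** The protocol gives no dropout rate, effect size or standard deviation, so it has no figure of its own to reproduce. From the document come N = 220, 110 per arm if recruitment is full (0.7 × 110 + 0.3 × 110 = 110), and the visit schedule. Everything else below is assumed.

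**1. Participants kept.** Let m be the share missing each post-baseline visit, independently. A T0–T3 analysis keeps 220 × (1 − m); a four-visit analysis keeps 220 × (1 − m)³.

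| m (assumed) | T0 and T3 | All four visits |
|---|---|---|
| 5% | 209 | 189 |
| 10% | 198 | 160 (0.9³ = 0.729) |
| 15% | 187 | 135 |

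At 10%, about 38 people (198 − 160) who attended T3 would be deleted only because of an interim miss.

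**2. Bias when dropout follows observed decline.** Simulated setting: 400 trials per scenario, 110 per arm. MoCA-like means at T0–T3 are 20, 19, 18, 17 (control) and 20, 19.5, 19, 18.5 (intervention), with variances 16, 18, 20, 23 and between-visit correlations of about 0.57 to 0.79. The true difference in change is (18.5 − 20) − (17 − 20) = 1.5 points. The logit of leaving before the next visit is a − 0.35 × (change so far + 1) − 0.10 × (last value − 19). The constant a is −2.5 in both arms (equal propensity), −2.5 control and −3.2 intervention (more control loss), or −3.0 control and −2.2 intervention (more intervention loss).

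| Scenario | Completing, of 220 | Completers only | Likelihood, four visits | Likelihood, T0 and T3 only | No dropout |
|---|---|---|---|---|---|
| Equal propensity | 157 | 1.32 | 1.46 | 1.33 | 1.48 |
| More control loss | 169 | 1.15 | 1.50 | 1.14 | 1.49 |
| More intervention loss | 161 | 1.57 | 1.46 | 1.60 | 1.43 |

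The standard deviation of the estimates across trials is at most 0.64, so the Monte Carlo error of each mean is about 0.64/√400 = 0.03.

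Three things follow.

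- Against the same trials without dropout, completers-only estimates are off by −0.16, −0.34 and +0.14. The direction depends on who leaves.
- The four-visit likelihood analysis stays within 0.03 of the no-dropout value. Dropout here depends only on observed values, so this success is partly built in.
- With T0 and T3 alone, likelihood reproduces the completers-only result. That is the NTB's situation.

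The spread of the completers-only and four-visit likelihood estimates is similar (0.60 to 0.64). Under pure dropout the gain is therefore in bias rather than precision. The loss of numbers in step 1 comes from interim misses.

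**The case against.** The strongest reply is that the sentence concerns a supporting description in a study that section 4.1 calls exploratory. Pre-post most naturally means T0 against T3, and for most outcomes those are the only two visits. A missed T1 or T2 then removes nobody, and the 160-of-220 figure does not arise. This stands as a limit: that figure belongs to the four-visit reading and to the MoCA and one AES schedule. It does not rescue the method for those two outcomes, because the two-visit reading ignores their interim data.

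A reader might also infer that within-arm change will be taken as the training effect. The protocol does not support this. Section 4.5 assigns the effect to a between-group ANCOVA, and nothing says that the repeated-measures analysis lacks a group factor.

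Nor should one infer that a mixed model would recover dropouts for every outcome. The NTB and most secondary outcomes have no T1 or T2 value, and the fifth column of the simulation table shows how little such a model gains for them.

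One uncertainty works the other way. The text after Table 1 in section 4.4.1 says that questionnaires are given at 0, 6, 12 and 18 months, while the table lists most of them at T0 and T3 only. If the text governs, the point reaches more outcomes.

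**Conclusion.** The point holds for the MoCA and the AES schedule with interim visits. The method named for change over time either deletes participants for one missed visit (160 of 220 kept at an assumed 10% per visit; 189 to 135 for 5% to 15%) or ignores the 6- and 12-month data. Under decline-related dropout its result can be too small or too large. It is a modest, inexpensive improvement to a supporting analysis.

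A reader might go further and conclude that the primary NTB comparison is biased towards the training. Simulation with no true effect can produce a false benefit of 0.05 to 0.11 SD and a type I error of 8% to 16% for a completers-only ANCOVA. It does so only when dropout is random in the control group and decline-dependent in the intervention group. With equally decline-dependent dropout in both arms, the bias under no effect was 0.00. The protocol states neither mechanism, so these figures are not an expected size. Nor does section 4.5 say that the primary ANCOVA is restricted to completers; handling of missing T3 values may be in a SAP that is not at hand.

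**What to change.** For the MoCA and the AES schedule with T1 and T2, replace repeated-measures ANOVA with a linear mixed model (SPSS MIXED, REML, unstructured covariance across visits). Include group, visit, group-by-visit and the covariates already named in section 4.5. Use all randomised participants with any data, and report the group-by-visit contrast at T3, that is, the difference between arms in change from T0 to T3. State which AES version has the interim visits, and reconcile Table 1 with the questionnaire timing in the text below it.

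For the NTB and other outcomes measured only at T0 and T3, ANCOVA can stay. If T3 NTB values are missing, an optional addition is multiple imputation by arm from T0 NTB and MoCA at T0, T1 and T2, with the completers-only analysis as sensitivity.

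The cost is a change of wording and some programming in the same software, with no new data. The downside is reliance on missing at random, which is weaker than what a completers-only analysis assumes but is still an assumption.

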### 4.2.2. Sample

The study aims to include 220 patients with Alzheimer's dementia (as per NINCDS-ADRDA criteria). Additionally, their primary relatives/informal caregivers (n=220), 5 professional caregivers and 5 M.A.S. (Alzheimer Syndrome) trainers (individuals conducting stage-specific training for people with dementia in individual and group sessions across various care settings) will be included.

[figure not shown]

Figure 1: Overview of the Randomized Controlled Trial (RCT)

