#### 4.2.2.1. Inclusion and Exclusion Criteria

##### People/Person with Dementia (PwD)

###### Inclusion Criteria:

- A diagnosis of possible or probable dementia according to NINCDS-ADRDA criteria (McKhann et al., 2011).
- The person with dementia (PwD) is over 40 years old at the baseline assessment.
- The PwD speaks and understands German and possesses sufficient physical, auditory, and visual abilities to undergo a neuropsychological examination and participate in tablet-based training.
- The PwD has been receiving stable medication therapy for at least 3 months prior to the baseline visit.
- Memantine therapy must have started at least 3 months before the baseline visit.
- A relative/informal caregiver accompanies the PwD to the neurological examination at the University Clinic for Neurology at T0 and T3.
- If the PwD has paid 24-hour care, a relative must be recruited as a participant/informal caregiver.
- The PwD lives with or without a relative/informal caregiver at home (if alone, relatives/informal caregivers should live nearby).
- The PwD has professional (e.g., home nursing care) and/or informal care (e.g., by relatives) or receives no care.
- The PwD is capable of giving consent or a relative with representation authority or legal guardian provides consent to participate in the study.
- The PwD is not taking antipsychotics or antidepressants, or has been stabilized on these medications for at least 14 days before the study start.

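### Repeated-measures ANOVA adjusted for age: unless age is centred, the SPSS time test refers to a person aged 0 and not to the average pre-post change (minor; secondary analysis only)

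*Protocol*

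**What the plan says.** Protocol section 4.5 (Statistics, Quantitative Part) fixes three things in one paragraph.

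- Software: "The data will be analyzed using IBM SPSS version 24".
- Method for change and, in the very next sentence, adjustment: "Pre-post comparisons (ANOVA repeated measures) will provide insights into changes over time. Analyses will be adjusted for age, gender, comorbidities, and education level". Nothing restricts the adjustment to particular models.

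The primary comparison, the global score of the neuropsychological test battery between intervention and control, is assigned to ANCOVA in the same paragraph. The protocol does not say whether covariates are centred, whether education and comorbidities are numeric or categorical, or which term of the repeated-measures model will be read.

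Two further facts matter. Section 4.2.2.1 requires that the participant "is over 40 years old at the baseline assessment", and section 4.2.2 sets the size: "The study aims to include 220 patients with Alzheimer's dementia".

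**The concern.** The natural reading of 4.5 is a repeated-measures model with person-level covariates, used to describe change over time. In the SPSS repeated-measures procedure covariates are used as entered. Once a numeric covariate is in the model, the time main effect is no longer the average within-person change. It is the change predicted where that covariate equals zero. For age, that is an extrapolation far below any eligible participant.

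In a trial lasting 1.5 years in a progressive disease, a reader will take the time p-value as evidence that patients did or did not change on average. If the test answers another question, real decline can go undetected, or a significant result can appear when mean change is nil. The estimated marginal means printed beside it would be taken at the covariate means by default, so the p-value and the displayed means would refer to different quantities.

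**Working it through.** The protocol gives no power calculation, SD or age distribution, so there is no figure of its own to reproduce.

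**Inputs from the protocol.** n = 220 (section 4.2.2); equal arms of 110 (section 1); significance level 0.05 (section 4.5), taken as two-sided; age over 40 (section 4.2.2.1).

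**Assumptions.** Age mean 75, SD 8, varied from 70 (SD 10) to 78 (SD 6). Residual SD of the change score = 1, so effects are in SD units. Age slope of change 0, -0.02 or +0.02 SD per year. No dropout. Group and gender effect-coded.

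**Step 1: what is tested.** With two time points (the test battery is given at baseline and at 18 months), let D = post minus pre. The time main effect equals the intercept test in

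D = b0 + b1·group + b2·gender + b3·age + error.

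With age as recorded, b0 is the mean change at age 0. With age minus its sample mean, b0 is the mean change at the average age. The estimate and test of b1, which is group-by-time, are the same either way.

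**Step 2: standard error.** Relative to the centred model, the SE of b0 is multiplied by about sqrt(1 + (mean age / SD age)²).

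- 75/8: sqrt(1 + 9.375²) = 9.43
- 70/10: sqrt(1 + 7²) = 7.07
- 78/6: sqrt(1 + 13²) = 13.04

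Centred SE = 1/sqrt(220) = 0.067. Raw SE for 75/8 = 9.43 × 0.067 = 0.636.

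**Step 3: power with no age slope.** The standardised effect is decline/SE.

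| True decline | Centred | Power | Raw age (75/8) | Power |
|---|---|---|---|---|
| 0.3 SD | 0.3/0.067 = 4.45 | 99% | 0.3/0.636 = 0.47 | 8% |
| 0.5 SD | 0.5/0.067 = 7.42 | >99.9% | 0.5/0.636 = 0.79 | 12% |

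For 0.3 SD with raw age, power is 10% at 70/10 and 6% at 78/6.

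**Step 4: change depends on age, true mean change zero.** The contrast at age 0 is 0 - slope × 75. A slope of -0.02 gives +1.5 SD, and +0.02 gives -1.5 SD. Dividing by the SE, 1.5/0.636 = 2.36, so the raw test rejects in about 65% of trials for either slope. The centred test rejects in about 5%. Over the age range the raw figure runs from 83% (70/10) to 42% (78/6).

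**Step 5: both together.** With a true decline of 0.3 SD and slope -0.02, the contrast at age 0 is -0.3 + 1.5 = +1.2 SD, and 1.2/0.636 = 1.89. About 47% of trials then reject with the contrast pointing to improvement. With slope +0.02 it is -0.3 - 1.5 = -1.8 SD: right direction, six times too large.

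**Step 6: simulation.** 4,000 trials per setting, age as the only numeric covariate. Raw against centred rejection was 7% against 99% (decline 0.3, no slope), and 65-66% against 5% (no mean change, slope of 0.02 either way). The group-by-time statistic was identical in every replicate.

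**Step 7: further numeric covariates.** Adding education in years (assumed mean 9 to 11, SD 3) takes the SE multiplier to between 7.7 and 13.5. Age alone produces almost all of it.

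**The case against.** The best reply is that the protocol never says covariates go in uncentred. Centring and coding are details commonly left to a statistical analysis plan, which is not at hand. That stands as far as it goes: the text is silent on centring and does not prescribe a wrong test. But it does prescribe adjusting, in named software, a model meant to show change over time, and that instruction is safe only if an unstated step is added.

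It can also be said that the pre-post method is called ANOVA, not ANCOVA, and that the adjustment sentence is general. Its position directly after the pre-post sentence, with no restriction, makes the wider reading the natural one, though not the only one. Nor does the protocol say that the time main effect will be read. If the analyst reads group-by-time, centring changes nothing.

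Three stronger readings are tempting and are not supported.

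- *The test is taken at zero education and zero comorbidities.* The protocol speaks of a level of education and of comorbidities, which may be categorical. Entered as factors, they are averaged over and raise no such problem. The case rests on age.
- *The analysis will show change with the wrong sign.* An F-test has no sign, and the default marginal means in SPSS would show the actual direction. A reversed contrast also needs a negative age slope, which the documents do not give. What holds is that the p-value and the reported mean change come apart.
- *The adjustment serves no purpose in these models.* For group-by-time, covariates can reduce residual variance and handle imbalance between arms. That is relevant because section 4.2.2.3 moves allocation from 70:30 to 30:70 during enrolment.

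**Conclusion.** The point holds in conditional form. If age is entered as recorded, the time main effect in the planned repeated-measures models is evaluated at age 0 and is not a test of average pre-post change. Under the central assumptions the standard error is about 9 times too large, power for a 0.3 SD decline drops from about 99% to about 8%, and false rejection is about 65% when change varies with age by 0.02 SD per year. Every age mean, SD and slope behind these figures is assumed. Over the ages tried, power for that decline stays between 6% and 10%.

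A reader might infer that the trial's answer on effectiveness is at risk. It is not: the primary between-group ANCOVA does not use this term, and group-by-time is numerically unchanged. This is a minor point about a secondary analysis in a study that section 4.1 calls exploratory.

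**What to change.** Add one sentence to section 4.5: in every repeated-measures model, continuous covariates are centred at their sample mean before entry. An equivalent is to state that change over time is tested by contrasts of estimated marginal means evaluated at the covariate means. Keep the covariates in the model, since group-by-time may benefit from them. The cost is one sentence and one compute step per numeric covariate in SPSS. No data collection, sample size or group comparison changes.
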